# Does a new spatial design in psychiatric inpatient care influence patients’ and staff’s perception of their care/working environment? A study protocol of a pilot study using a single-system experimental design

**DOI:** 10.1186/s40814-018-0383-4

**Published:** 2018-12-26

**Keywords:** Activity, Environment, Feasibility, Intervention, Nursing, Process evaluation, Protocol, Single-system design, Psychiatric inpatient care, Quality interactions

## Abstract

**Background:**

Research shows that worn-out physical environments are obstacles to psychiatric inpatient care. Patients want better relationships with staff and things to do; staff want an environment that offers hope, a calm atmosphere, and joint activities. A county council in northern Sweden and Philips Healthcare partnered to create solutions to the environmental challenges of psychiatric inpatient care. One ward at a county psychiatric clinic was selected for a pilot project to test solutions that could improve the care environment for patients, staff, and relatives. The aim of the overall project is to evaluate the effects of a newly designed psychiatric inpatient ward on patients and staff in terms of quality of care and stress. In this study, we focus on the feasibility through testing questionnaires and exploring barriers to recruiting staff and patients.

**Methods:**

This study had a single-system experimental design, comparing a psychiatric unit pre- and post-implementation of the novel spatial design, using repeated measures with the same questionnaires twice a week during baseline and intervention phases. Primary outcomes were quality interactions (patients) and perceived stress (staff). Secondary outcomes were levels of anxiety and depression (patients), and stress of conscience (staff). A process evaluation was aimed to describe contextual factors and participant experiences of the new design. Data was collected using questionnaires and semi-structured individual interviews with patients and focus group discussions with staff. Both visual and statistical methods were used to analyse the quantitative data and content analysis for the qualitative data.

**Discussion:**

The findings will contribute insights into whether and how a new spatial design might contribute to quality interactions and reduced stress. This is relevant both nationally and internationally, as similar interventions are needed but sparse. The findings will be disseminated through peer-reviewed publications and conference presentations.

**Trial registration:**

ClinicalTrials.gov, NCT03140618, registered 4 May 2017

## Background

In 2015, 105,000 admissions to psychiatric inpatient care were recorded in Sweden, more than in previous years. It was also reported that patients in psychiatric inpatient care experienced poorer treatment and participated less in their healthcare than patients in somatic care [1]. Research shows that a psychiatric inpatient care ward should offer a positive atmosphere supported by an environment characterised by structure and flexibility [2–4]. Other important issues are peace, security, safety [5–9], and access to personal spaces [5, 6, 8]. Borge and Fagermoen [9] showed that an appealing, comfortable, and pleasant physical environment that felt safe and warm helped patients feel more at ease and increased their sense of self-worth and will to live, prerequisites to feeling better. Noble and Rowland [10] also reported that feeling comfortable in the environment can improve patients’ confidence, and ability to express themselves, and discovery of personal interests and opportunities.

Lindgren et al. [11] showed that patients described the environment in psychiatric inpatient care as confusing, with inconsistent procedures and regulations. There was limited space to relax and patients could not protect themselves from hearing and observing unpleasant events. Similarly, Molin et al. [12] found that patients in psychiatric inpatient care reported feeling their environment to be more stigmatising than protective. The wards were described as worn out, poor, and dirty. This made the patients feel less valued than patients treated in other specialties. Negative perceptions of the environment have also been reported by staff in the same context. In another study by Molin et al. [13], staff described that they had to represent an environment that they could not defend. They described a poor and worn out environment that in their experience had a negative impact on patients’ mental health. They wanted to offer an environment that gave hope and made them proud of their work, but instead, they felt that psychiatric inpatient care had a lower priority than other healthcare specialties.

It can be concluded that a worn-out physical environment constitutes an obstacle to psychiatric inpatient care, and that the aesthetic dimension of healthcare should be highlighted. In these situations, patients and staff share negative perceptions of the environment [12–15], leading to counterproductive care and experiences of stigmatisation among patients [12, 16]. Patients want more human relationships with staff and interesting things to do, while staff want an environment that inspires hope, creates a calm atmosphere, and offers opportunities for joint activities [17, 18].

### The light and environmental project

In 2014, a county council in northern Sweden and Philips Healthcare formed a partnership to create new innovative solutions to the environmental challenges in psychiatric inpatient care. One ward at a county psychiatric clinic was selected as a pilot project to test solutions that could improve the care environment for patients, staff, and relatives. The project was performed in several phases, beginning with an analysis of the existing facilities using a field survey and available health and environmental data. Based on the findings, a new spatial design was developed including healing lights, a sensory room, and space for physical activity. Construction of the new ward began in spring 2016 and was completed in the autumn of 2017.

Healing lights have been shown to have beneficial effects for both patients and staff. A system of lighting that automatically follows the circadian rhythm and includes multicolour elements controlled by the patients can enhance their sleep duration, mood, and general satisfaction [19]. In recent years, interest in sensory rooms has increased in many different healthcare environments, such as dementia care, brain injury rehabilitation, habilitation for people with learning disabilities, and psychiatric inpatient care [7, 20–22]. Sensory rooms are used in psychiatric inpatient care to offer patients an environment that stimulates the senses without being too demanding [20] and a room for relaxation, stress reduction, and the opportunity to develop self-soothing skills [21]. The rooms include elements such as light, paintings, photographs, coloured walls, aromatic oils, music, movies, ball quilts, textiles, and comfortable furniture [7, 20, 21, 23, 24].

The physical activity room is a social area for movement that also contains a selection of exercise equipment. Physical activity and exercise are positively related to mental health and well-being [25, 26], and research shows that such activity can help to increase self-esteem [27, 28], decrease anxiety [29], provide structure to a person’s day or week, contribute to a sense of purpose and meaning in daily life [30], and provide opportunities for social experience, commitment, and interaction [31].

### Study aim

The aim of the overall project is to evaluate the effects on quality of care and stress in patients and staff resulting from a new spatial design for a psychiatric inpatient ward. In this study, we focus on the feasibility of the project, and the objectives are to test the questionnaires and explore barriers to the recruitment of staff and patients.

#### Feasibility objectives

The feasibility objectives are to discern the following:The properties of the questionnaires regarding detection of change;Whether the chosen questionnaires are suitable for frequent measurements; andThe plausible recruitment rates for this study.

#### Research questions

The following questions will be answered:Does the new spatial design influence the quality of interactions between staff and patients?Does the new spatial design influence patients’ mental health?Does access to a space for physical activity influence patients’ levels of physical activity?Does access to a sensory room influence patients’ mental health?Does a new spatial design influence staff levels of perceived stress and stress of conscience?Does a new spatial design influence the general activity level among patients and staff?Does a new spatial design influence the prevalence of coercive measures, use of PRN (as needed) medication, mean length of hospital stay for patients, and sick leave among staff?How do patients and staff describe their perception of the new spatial design, and how do contextual factors influence the possible changes?

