### Procedure

In the overall project, the evaluation will consist of two phases (A and B), and a follow-up, in line with the SSED. Baseline measures will be established during phase A, through outcomes measured twice a week for approximately 5 weeks. During these 5 weeks, staff and patients will not be introduced to the new environment. In phase B, staff and patients will be introduced to the new environment, and outcomes will be measured once a week over a period of 2 months.

The semi-structured focus group interviews with staff will be conducted at the end of phase B while patients will be interviewed individually very near to their discharge from the ward during phase B. Follow-up studies are planned for 6 and 12 months after phase B through interviews investigating whether the possible effects of changing the healthcare environment are sustainable [33].

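### The third and fourth research questions ask what the activity space and the sensory room each do, but the single switch to a bundled redesign cannot attribute a change to either room

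*Protocol article*

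**What the plan says.** The Research questions section of the protocol article lists eight questions and commits the study to answering them. Two concern one component each. The third asks "Does access to a space for physical activity influence patients" in their level of physical activity. The fourth asks "Does access to a sensory room influence patients" in their mental health. Beside them stand questions about the whole redesign in the same outcome domains: the second asks about patients' mental health, and the sixth asks "Does a new spatial design influence the general activity level among patients and staff".

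The intervention is described under The light and environmental project as a single package: "a new spatial design was developed including healing lights, a sensory room, and space for physical activity". It was built as one project: "Construction of the new ward began in spring 2016 and was completed in the autumn of 2017".

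Under Procedure, "the evaluation will consist of two phases (A and B), and a follow-up". Of phase A it says: "During these 5 weeks, staff and patients will not be introduced to the new environment". Of phase B it says that "staff and patients will be introduced to the new environment". Setting adds that phase A takes place on a temporary adjacent ward and phase B on the rebuilt ward. Methods makes the ward its own control. Analysis, Quantitative data, takes the mean over all respondents at each time point and compares the phases by visual inspection and a non-overlap percentage.

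**The concern.** The list of questions treats the effect of a room and the effect of the redesign as separate things to be learned. The design offers one before-and-after comparison in which everything changes together. If patients' mental health improves in phase B, that comparison cannot say whether the sensory room, the lighting, the activity space or the move from the temporary ward was responsible. The article itself names rival explanations: its background section credits lighting with effects on mood, and physical activity with effects on anxiety and well-being.

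What is at stake is the conclusion drawn. The Discussion hopes that the evaluation can guide other wards planning a similar redesign. A ward choosing which element to build could take an answer to the fourth question as evidence for a sensory room, when the data speak only to the package.

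**Working it through.** The plan states no figure on this point, so there is none to reproduce. The check is whether the described design can identify the effects that the questions name.

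**Inputs**
- Components: lighting, sensory room, activity space (The light and environmental project).
- A further change at the same boundary: the move from the temporary ward to the rebuilt one (Setting).
- Exposure: no part of the new environment in phase A, the rebuilt ward in phase B (Procedure, Setting).
- Data: one ward mean per instrument and time point, patients and staff separately (Analysis).
- Time points: the article's schedules differ, so three were tried. Table 1 gives 5 in A and 10 in B. Procedure gives twice weekly for 5 weeks (2 × 5 = 10), then weekly for 2 months. Questionnaires gives twice weekly in both phases. Taking 2 months as 2 × 52/12 = 8.7 weeks (an assumption), phase B has about 9 points weekly or 17 points twice weekly.

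**Model.** Let P be 0 at every phase A point and 1 at every phase B point. Each component's on/off indicator equals P, and so does the indicator for the move. The expected ward mean at time t is

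E(Y) = b0 + bL·P + bS·P + bA·P + bM·P = b0 + (bL + bS + bA + bM)·P,

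with L for lights, S for sensory room, A for activity space and M for the move. Only b0 and the sum in brackets can be estimated.

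**Rank of the design matrix**

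| Time points (A + B) | Level model: columns / rank | With trend and trend-by-phase: columns / rank |
|---|---|---|
| 5 + 10 | 5 / 2 | 7 / 4 |
| 10 + 9 | 5 / 2 | 7 / 4 |
| 10 + 17 | 5 / 2 | 7 / 4 |

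In the level model, five parameters rest on two independent columns, the intercept and P. The two trend terms add a common slope and one change of slope, which again belongs to the package. In both models the four changes share one level shift. More time points or more patients per point make the shift more precise but do not divide it.

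**The planned methods.** Visual comparison of level and trend, and the non-overlap percentage, use only the phase labels and the ward means. They carry no information on which room was responsible.

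**What separation would need.** For illustration, suppose the sensory room opened a third of the way through phase B and the activity space two thirds of the way through, with the lights on from the start. The matrix of intercept and three components then has 4 columns and rank 4 under all three schedules, so the effects are separable in principle. The article describes nothing of this kind.

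**The case against.** The strongest reply is that this is a feasibility pilot. Study aim limits the present study to testing questionnaires and exploring recruitment, the primary outcomes are interaction quality and staff stress, and the Discussion speaks of changes possibly related to the design as a whole. That limits the consequence. It does not remove the mismatch, because the Research questions section still commits to answering both component questions.

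A second reply is that the interviews and process evaluation will cover the rooms. They can describe how people perceive a room. They do not isolate its effect on a questionnaire score or an activity measurement.

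A third is that no sentence says that all components open together. That is correct. It is an inference from the completed construction, the unexposed phase A and the phase B on the rebuilt ward. Nothing suggests staging.

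A reader might also infer more than the article supports:
- **That no data on room use are planned.** Table 1 lists ward observations at measurements 10 to 15 without describing them. They may or may not record use.
- **That crowding fell, as a further rival explanation.** Setting says only that the ward could add 5 beds to its 13 and that the rebuilt ward cannot. It does not say that extra beds were in use during phase A.
- **That the second and fourth questions rest on the same anxiety and depression score, and the third and sixth on the same activity measure.** The article assigns no instrument to any question. Patients also complete a functioning scale (ORS), and the monitor yields several measures. The sixth question also includes staff. Whichever measure is used, the component still cannot be separated.
- **That all explanations are equally supported.** Being inseparable in these data does not make them equally plausible.

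**Conclusion.** The concern holds as a mismatch between two questions and the design that is meant to answer them. As described, the study can estimate at most one phase A to phase B change per outcome for the redesigned ward together with the move. It cannot attribute a change in mental health to the sensory room, or a change in activity to the activity space, at any sample size. Two of the eight questions are affected. The whole-design questions do not fall to this argument.

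The conclusion assumes that the components became available together at the start of phase B, as the article implies. It does not depend on which measurement schedule is followed, on which instrument answers which question, or on whether room use is observed. Use records would be self-selected, and the planned analysis works on ward means.

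**What to change.** Restate the third and fourth questions as effects of the redesigned ward as a whole, or recast them as descriptive questions about the two rooms for the interviews and process evaluation. Add one sentence saying that no component-specific effect will be claimed from the phase comparison.

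This means rewording two questions and adding a sentence. It needs no new data and can be done even if collection has finished. The price is a narrower claim.

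A room-use log compared with outcomes day by day is not a workable substitute. The anxiety and depression scale is completed once or twice a week, and Table 1 places the activity monitor at only two phase B points (10 and 11). Linking individual use to individual scores would also be a new analysis, because the plan uses ward means.

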## Methods

This is an intervention project using a single-system experimental design (SSED) with baseline and intervention phases [32]. SSED studies focus primarily on changes in one system (in this case the ward), and the system works as its own control. As single-system designs aim to detect changes within each system rather than to compare systems, sample sizes in this tradition are relatively small and no sample size calculations are made [33]. Data for the system will consist of aggregated measurements from patients and staff respectively on the ward [32, 33]. This means that the total number of individuals included in the study depends on (a) the number of patients admitted to the ward at each point of measurement and (b) the number of staff members working on the ward. In parallel, a process evaluation is performed to describe patient experiences and important contextual factors.

### Procedure

In the overall project, the evaluation will consist of two phases (A and B), and a follow-up, in line with the SSED. Baseline measures will be established during phase A, through outcomes measured twice a week for approximately 5 weeks. During these 5 weeks, staff and patients will not be introduced to the new environment. In phase B, staff and patients will be introduced to the new environment, and outcomes will be measured once a week over a period of 2 months.

The semi-structured focus group interviews with staff will be conducted at the end of phase B while patients will be interviewed individually very near to their discharge from the ward during phase B. Follow-up studies are planned for 6 and 12 months after phase B through interviews investigating whether the possible effects of changing the healthcare environment are sustainable [33].

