#### Questionnaires

During both phases, measurements will be taken twice a week, with an assigned staff member distributing the questionnaires to the participants. Based on results from previous research [12, 34] showing that experiences of interactions with staff are related to experiences of the physical environment, the primary outcome measure for patients will be the perceived quality of their interaction with the staff. Secondary outcome measures will be levels of depressive symptoms, anxiety, satisfaction, and quality of care.

Based on results from previous research [13, 35, 36] showing that staff in psychiatric inpatient care experience stress related to inadequate physical environments, the primary outcome measure for staff will be perceived stress. Secondary outcome measures will be stress of conscience and quality of care. Demographic data will be collected for all participants.

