##### Semi-structured interviews

Both patients and staff will be interviewed by the researchers in semi-structured interviews [50]. Patients will be interviewed individually while staff will participate in focus groups. During phase B, patients will be interviewed very near to their discharge from the ward, while the focus group interviews with staff will be conducted at the end of phase B. The participants will be asked to share their experiences of the ward environment and its impact on the quality of their interactions. Staff will also be asked about the ward environment’s impact on their daily work and perceived stress. Table 1 shows a flowsheet of the data collection.

**Table 1 Tab1:** Modified SPIRIT-figure showing intervention and data collection flowsheet

Intervention phase	A					B									
Measurement no.	1	2	3	4	5	6	7	8	9	10	11	12	13	14	15
Assessments, patients															
CPS	●	●	●	●	●	●	●	●	●	●	●	●	●	●	●
ORS	●	●	●	●	●	●	●	●	●	●	●	●	●	●	●
HAD	●	●	●	●	●	●	●	●	●	●	●	●	●	●	●
QPC-IP	●														●
Interviews												●	●	●	●
Activity monitor		●	●							●	●				
Assessments, staff															
PSS	●	●	●	●	●	●	●	●	●	●	●	●	●	●	●
SCQ	●	●	●	●	●	●	●	●	●	●	●	●	●	●	●
QPC-IPS	●														●
Interviews												●	●	●	●
Activity monitor		●	●							●	●				
Observations at ward										●	●	●	●	●	●

*●*Measurement performed, *CPS* Caring Professional Scale, *ORS* Outcome Rating Scale, *HAD* Hospital Anxiety and Depression Scale, *QPC-IP* Quality in Psychiatric Care–Inpatient, *PSS* Perceived Stress Scale, *SCQ* Stress of Conscience Scale, *QPC-IPS* Quality in Psychiatric Care–Inpatient Staff, Supplementary data from ward registers will be collected continuously

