### Analysis

#### Quantitative data

Demographic data for participants will be presented as means and proportions. In the SSED research tradition, focus is on changes within subjects, not between groups [33]. Thus, traditional inferential statistics are rarely used. Visual and numerical methods will be used to analyse data from the SSED study [51]. Visual inspection of the data requires comparing levels, trends, and changes between intervention phases [33]. Also, the percentage of non-overlapping data statistics will be calculated, i.e. the percentage of phase B data that overlaps with the most extreme data point in phase A [33]. In this study, data from patients and staff will be analysed separately. Measurement data for each of the questionnaires will consist of the mean ratings from all participants, patients, and staff respectively, answering at each point in time.

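### Three conflicting questionnaire schedules: under the one in Procedure, measurement frequency halves exactly when the ward changes

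*Protocol article*

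**What the plan says.** Procedure gives each phase its own frequency and length. Phase A is described as "outcomes measured twice a week for approximately 5 weeks"; for phase B, "outcomes will be measured once a week over a period of 2 months".

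Two other places give one frequency for both phases. The Abstract (Methods) describes the design as "using repeated measures with the same questionnaires twice a week during baseline and intervention phases". The Questionnaires section says "During both phases, measurements will be taken twice a week".

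Table 1, titled "Modified SPIRIT-figure showing intervention and data collection flowsheet", has 15 measurement columns: 1 to 5 under phase A and 6 to 15 under phase B. CPS, ORS, HAD, PSS and SCQ are marked at every one.

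Three other parts of the article bear on the point:

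- The opening of Methods makes the ward its own control. Setting places phase A on the relocation ward and phase B on the rebuilt ward.
- The Quantitative data section takes the mean over everyone who answers at an occasion as the data point, and adds: "Visual inspection of the data requires comparing levels, trends, and changes between intervention phases".
- The second feasibility objective is "Whether the chosen questionnaires are suitable for frequent measurements"; the third concerns plausible recruitment rates.

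**The concern.** With no concurrent comparison ward, anything that changes at the A-to-B switch cannot be separated from the new spatial design. The measuring procedure is one thing the investigators can hold constant. Procedure, read alone, changes it at that very moment and gives no reason.

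Four things would then change together with the ward: the questionnaire load on people rating their own stress and interactions, the spacing of the points whose trend is inspected, the number of distinct short-stay patients who are ever measured, and the intensity at which the questionnaires are tried out. The last two touch the feasibility objectives directly.

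The conflict between the sections matters for the same reason. Someone reconciling them could settle on Procedure because it is the most detailed text, and so build the confounding in.

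**Working it through.** **1. Occasions implied by each source** (frequency × weeks; phase A about 5 weeks; 2 months taken as 8-9 weeks)

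| Source | Phase A | Phase B | Per week, A | Per week, B |
|---|---|---|---|---|
| Procedure | 2 × 5 = 10 | 1 × 8-9 = 8-9 | 2 | 1 |
| Abstract and Questionnaires, with Procedure's phase lengths | 2 × 5 = 10 | 2 × 8-9 = 16-18 | 2 | 2 |
| Table 1 | 5 | 10 | 5/5 = 1.0 | 10/9 to 10/8 = 1.1-1.25 |

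Table 1's 5 and 10 cannot be reproduced from either text. Weekly measurement in both phases (5 and 8-9) comes closest, but no section states weekly measurement in phase A. Only Procedure yields a 2:1 change.

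Steps 2 to 4 apply only if Procedure is followed.

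**2. Staff load.** Staff-related questionnaires gives the PSS 10 items and the SCQ nine items of two parts each: 10 + 9 × 2 = 28 responses per occasion. That is 2 × 28 = 56 a week in A and 1 × 28 = 28 a week in B, a fall of 50%.

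**3. Trend.** Points are on average 3.5 days apart in A and 7 days apart in B. A constant drift of b per week is b × 3.5/7 = b/2 per measurement in A and b × 7/7 = b in B. On an axis of measurement number the slope doubles at the move with no effect of the ward. On an axis of calendar days it does not.

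**4. Distinct patients measured.** Assume admission times uniform over the week and gaps of 3 and 4 days in A. For a stay of L days, the chance of being present at one or more occasions is [min(L,3) + min(L,4)]/7 in A and min(L,7)/7 in B.

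| Stay (days) | A | B |
|---|---|---|
| 2 | 4/7 = 57% | 2/7 = 29% |
| 3 | 6/7 = 86% | 3/7 = 43% |
| 4 | 100% | 4/7 = 57% |
| 5 | 100% | 5/7 = 71% |
| 7 or more | 100% | 100% |

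The article gives no length-of-stay distribution, so the overall effect cannot be computed. It is confined to stays under 7 days.

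**5. Under the Abstract and Questionnaires wording** every A:B ratio in steps 2 to 4 is 1 and the problem disappears.

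**6. What thinning the baseline would do.** If phase B stayed weekly and phase A were cut to matching weekdays, A would fall from about 10 points to about 5. With no effect and exchangeable points, the expected share of B points beyond the most extreme A point is 1/(n + 1), where n is the number of A points: 1/11 = 9% with 10 and 1/6 = 17% with 5. Thinning therefore makes the non-overlap statistic more favourable to apparent change.

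**The case against.** The strongest reply is that the halving is not the settled plan. Two sections say twice weekly throughout, and Table 1 shows roughly equal weekly rates. That stands: a reader of Procedure alone might infer that the protocol has fixed a halved frequency, and the article as a whole does not support this. The confounding is conditional on Procedure being the version carried out.

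Further objections also stand, in whole or in part:

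- **Short stays.** A reader might infer that missing short-stay patients biases the phase B outcome levels. It need not. Each data point averages those present and answering at that occasion, and the mix of stays on a given day does not depend on how many other rounds that week holds. The effect is on how many distinct patients are measured.
- **Recruitment.** Participants says that all admitted patients are informed and invited, so the proportion consenting need not change. The opening of Methods, however, ties the number included to patients admitted at each measurement point, so the yield can change.
- **Weekday.** A shift from averaging two weekdays in A and one in B is possible, but no measurement days are named, so it is inference.
- **Load and scores.** Nothing in the article shows that fewer forms would lower PSS or raise CPS. The change in load is certain under Procedure; its effect on scores is unknown.
- **Time axis.** Table 1 is a collection flowsheet, and the article does not say that graphs will use measurement number.
- **Frequent use.** The article does not define frequent. Weekly use in B would still inform the second objective, though not at the twice-weekly intensity.

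The feasibility aim, and the admission in the Discussion that the evaluation is less standardised than usual, lower the stakes. They do not explain a change of frequency at the move.

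**Conclusion.** The firm defect is a three-way conflict over the schedule: about 10 and 8-9 occasions (Procedure), 10 and 16-18 (Abstract and Questionnaires), or 5 and 10 (Table 1). It has a consequence beyond editing, because one of the three versions changes the measuring procedure together with the intervention.

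Under that version weekly staff load halves, a steady drift doubles in slope per measurement number, capture of patients staying under 7 days falls by up to half, and twice-weekly use is tried only on the relocation ward. The capture figures rest on the assumed uniform admissions and 3- and 4-day gaps; the slope artefact rests on plotting by measurement number. The documents do not show the size, or even the existence, of a resulting bias in PSS or CPS.

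The point should be corrected. It is cheap to remove, and the equal-frequency version is already stated in two places.

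**What to change.** Reconcile the Abstract, Procedure, Questionnaires and Table 1 to one schedule. State the same frequency and the same fixed weekday or weekdays in both phases for CPS, ORS, HAD, PSS and SCQ. Twice weekly is what the Abstract and Questionnaires already say. Add to the Analysis section that trends are plotted and compared on calendar days.

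The cost is a sentence each in Procedure and Analysis, a corrected Table 1, and about 8-9 more short questionnaire rounds in phase B than Procedure implies (16-18 instead of 8-9).

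If phase B has to stay weekly, give the reason, keep all phase A occasions in the main comparison, and add a sensitivity analysis restricted to phase A occasions on the phase B weekday. That restriction should not be the main analysis, because it leaves about 5 baseline points and favours apparent change in the non-overlap statistic.
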